# **2.3. Study Visits**

*2.3.1. Genetic education and counselling, questionnaires and phone interview (Stage 1, Cohort 1)*

Genetic education and counselling occurs over 2 study visits at the Clinical Research Facility, based at Princess Alexandra Hospital (CRF-PAH), or alternatively over 2 online video conference sessions using Zoom. Participant visits and contact points are detailed in Figure 1. The first counselling session will begin by discussing the PICF, answering any questions the participant may have, and gaining signed consent to continue with the study if the participant is happy to proceed. If counselling is being done by Zoom video conferencing, then the PICF will need to be signed and returned beforehand. Following this, the participant will be asked to complete a selection of validated questionnaires (see table 1). The purpose of these questionnaires is to capture the participant’s skin cancer knowledge, views and health behaviours prior to receiving genetic education and counselling. After completing the questionnaires, a genetic counsellor (or trained dermatologist) from the research team will conduct a pre-testing genetic education and counselling session that includes collection of personal and family medical history, education on genetics, the likelihood of detecting a mutation given the medical/family history and the possible impact of test results on the individual and their family members. At the end of this education and counselling session the participant will be asked again if they still wish to go ahead with the genetic testing, and if they do, a saliva sample will be requested. Participants will be asked if they would like to invite family members to join the study. If they do, then the genetic counsellor/dermatologist will identify specific family members that would meet the criteria for genetic testing, and therefore be eligible to join the study. Study brochures will be given to the participant to supply to family members. The visit will take between 1 to 1.5 hours in total.

In most cases the second counselling session for test reporting will occur approximately. 2-3 months after their first visit. This visit will either take place at the CRF- PAH or over online video conference call using Zoom, and will take approx. 1 to 1.5 hours. The session will begin by asking the participant to complete a questionnaire with selected validated instruments (see table 1). The purpose of these questionnaires is to measure any impact from the first genetic education and counselling appointment. Once questionnaires are complete, a genetic counsellor (or trained dermatologist) from the research team will conduct the post testing genetic counselling and reporting of genetic testing results. This process includes: test results, significance for personal risk, significance for family risk, recommended preventative health behaviour and screening. The genetic counsellor or dermatologist will offer to send a report of the genetic findings to the participant’s nominated healthcare provider. At the end of the counselling session, the participant will be asked if they consent to being contacted for a phone interview at a later date.

Post genetic testing, education and counselling questionnaires will be conducted at 2 weeks, 3 months and 12 months following reporting of test results. These questionnaires will be sent using the REDCap System, which facilitates an email containing a web-link to be sent for the participant to complete the questionnaire online, at their convenience. Two reminder emails to complete questionnaires will be sent out if not completed.

**Figure 1. A Flow chart of procedures involved for participants enrolled in Stage 1 of the study**

**Table 1: Questionnaires used at different time points.**

|  | Baseline (before counselling) | 2nd visit (before results) | 2nd visit (decliners) | 2 weeks | 3 months | 12 months |
| --- | --- | --- | --- | --- | --- | --- |
| **BACKGROUND INFORMATION** | | | | | | |
| Demographics | ✓ |  |  |  |  |  |
| Sun exposure | ✓ |  |  |  | ✓ | ✓ |
| Skin surveillance | ✓ |  |  |  | ✓ | ✓ |
| **HEALTH BELIEFS** | | | | | | |
| Risk perception^10, 21^ | ✓ | ✓ | ✓ | ✓ | ✓ | ✓ |
| Health Belief Model questionnaire^22, 23^ | ✓ |  |  |  |  | ✓ |
| Multidimensional Health Locus of Control (MHLC) Scale^24, 25^ | ✓ |  |  |  |  |  |
| **PSYCHOSOCIAL STATES AND TRAITS** | | | | | | |
| HADS (Hospital Anxiety and Depression Scale)^26^ | ✓ | ✓ | ✓ | ✓ | ✓ | ✓ |
| Cancer Worry Scale^27^ | ✓ |  |  |  | ✓ | ✓ |
| Fatalism Scale^28^ | ✓ |  |  |  | ✓ | ✓ |
| Belief in genetic determinism^29^ | ✓ |  |  |  |  |  |
| Monitor/Blunter scale^30, 31^ |  | ✓ | ✓ |  |  |  |
| State-Trait Anxiety Inventory (STAI)^32^ |  | ✓ | ✓ |  |  |  |
| **EXPERIENCE WITH GENETIC COUNSELLING AND TESTING** | | | | | | |
| Perceived benefits and limitations of genetic testing^10^ | ✓ |  |  |  |  |  |
| Genomic outcomes scale^33^ |  |  |  | ✓ |  |  |
| Genetic Counselling Satisfaction Scale (GCSS)^34^ |  | ✓ | ✓ | ✓ |  |  |
| Decision Regret Scale^35^ |  |  |  | ✓ |  | ✓ |
| Decision Satisfaction^36^ |  |  |  | ✓ |  |  |
| Perceived personal control (PPC)^37^ |  | ✓ | ✓ |  |  |  |
| MICRA (Multidimensional Impact of Cancer Risk Assessment)^38^ |  |  |  | ✓ | ✓ | ✓ |
| **DECLINING GENETIC TESTING** | | | | | | |
| Reasons for not testing^39, 40^ |  |  | ✓ |  |  |  |

*2.3.2. Semi-structured interviews (Stage 1, Cohort 1)*

A time and date convenient for the participant, will be organised to conduct the semi-structured interviews by phone call. The call will take approximately 30-60 minutes, and will take place approximately 1 month after genetic results were reported. At the start of the call, the researcher will check if the time/date is still convenient, and if it is not, they will reschedule. The interviews will be semi-structured, using a scripted guideline of questions. The interviews will be recorded using an audio recording device, with the participant’s permission.

*2.3.3. Cross-sectional Questionnaire (Stage 2, Cohort 2)*

This stage of the research will occur after all data is collected and analysed from Stage 1 of the research project. No study visit is required for Stage 2. We will use an online research platform, such as REDCap that will allow us to send an email to eligible participants, as described in recruitment (section 2.2.2). We will collect electronic consent for participation in Stage 2 of the study, before providing a link to the questionnaire to complete. This questionnaire can be completed at any time and it can be saved at any point to complete later. There will be no further follow up with participants in Stage 2, it will be a one-off (cross-sectional) questionnaire.

# **Genetic Counselling conducted by video conferencing (telegenetics)**

In line with measures for social distancing in response to the COVID-19 pandemic, we will now introduce an alternative to study visits at the Clinical Research Facility at PAH. For some participants we will conduct genetic counselling and education sessions via online video conferencing using Zoom (or similar), when possible. Prior to conducting the counselling session, a member of the research team will discuss the PICF in full over the phone with the participant and answer any questions. The participant will then need to sign the consent form and send it to us either by email or post. The counselling video-conferencing session will not occur until after the signed consent form has been received. After the counselling session, if the participant wishes to go ahead with testing, we will post them the self-collection saliva kit for genetic testing, with instructions on (pre-paid) postage for the sample.

A systematic review (Hilgart et al, 2012) of 12 separate studies has reported high levels of patient satisfaction with telegenetic services. Additionally when a comparison group was used, satisfaction levels were no different between those receiving face-to-face counselling.

# **Participants who decline genetic testing**

Some individuals may wish to take part in the research, but don’t wish to have genetic testing. Likewise, we expect that some participants may change their mind and decline genetic testing after receiving pre-testing genetic counselling and education, or decline receiving results after previously consenting to testing. We will ask these participants to remain in the study as they are valuable to our research in understanding barriers to genetic testing. For these participants, we will still provide genetic counselling and education based on their family history, rather than genetic testing (or not provide genetic test results if testing already completed). We would ask them to still complete pre and post questionnaires that measure their knowledge and perceptions on melanoma, psychological impact, and health behaviour. In addition we have a questionnaire designed to capture the reasons and motivation behind declining to genetic testing. We will also still invite them to take part in a semi-structured interview as part of Stage 1 of the research.

# **Dermatologist reporting genetic results**

Participants in Stage 1 of the study will be randomised to receive the genetic education, counselling and test reporting by either a genetic counsellor or a dermatologist (or dermatologically trained clinician). We will be using block randomisation, stratified by whether the participant is from a) CDKN2A positive family, or b) other familial melanoma mutation positive family, or c) no known melanoma mutation identified. Data linkage, descried in section five, will be used to identify the genetic status of past participants before randomisation to facilitate stratification.

The aim is to evaluate whether the person providing the genetic education and counselling (genetic counsellor or dermatologist), affects the psychosocial or behavioural outcomes. The dermatologists/clinician will be provided with training from genetic counsellors prior to providing genetic education, counselling and test reporting to participants. Questionnaire data collected throughout stage 1 of the study will be used to analyse any significant differences in psychosocial or behavioural outcomes.

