Currently, it is recommended that pre and post genetic education and counselling accompanies test reporting, and is provided by a qualified genetic counsellor. However, considering clinical genetic testing is very likely to increase quickly in the near future, it is important to acknowledge logistical implications and consider alternatives for clinical implementation. Counselling and reporting of genetic test results for the *BRCA1*/2 gene by trained nurses or doctors has become routine practice in several oncology clinics in Australia and the UK^16, 17^. Feedback from patients and nurses has been positive and this model provides improved access to genetic testing^16^. Testing and reporting on the *CDKN2A* gene variant is a candidate for mainstreaming the procedure in dermatology clinics. The advantages that a genetic counsellor has in delivering genetic test results is their expertise in dealing with complex issues of inherited risk, unexpected or incidental findings and inconclusive results such as ‘variants of unknown significance’. The mode of inheritance and risk significance is well understood for *CDKN2A*. Furthermore, a positive CDKN2A result would not be unexpected as a strong personal and family history of melanoma is a prerequisite for testing. With appropriate training on providing genetic education and counselling, testing for *CDKN2A* could become a standard procedure for a dermatologist. In most cases, a dermatologist will already know their patient’s personal and family history and are in the best position to offer subsequent recommendations based on test results, such as skin examination intervals. The present study will include a pilot study to produce preliminary data to explore this concept.

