# **1.2 Aims**

Primary Aim: To understand and describe the participant’s experience with genetic education, counselling and testing, and living with familial melanoma through qualitative analysis of semi-structured interviews.

Secondary Aims: To identify psychosocial and behavioural impact of genetic testing in familial melanoma, using quantitative analysis of validated questionnaires guided by the Health Belief Model as a theoretical framework. This will be achieved by;

1. Evaluate psychosocial and behavioural impact of genetic education, counselling (and testing) in individuals with a familial melanoma, regardless of whether a causal mutation has been identified.
2. Explore genetic fatalism in a subset of participants and whether they feel that genetic counselling (+/- testing) affected their beliefs.
3. Determine whether the person conducting the counselling session (genetic counsellor/dermatologist) affects psychosocial and behavioural outcomes.
4. Evaluate what psychological traits are associated with uptake of testing, psychological impact and behavioural change.
5. Assessment of the clinician training protocol, and supporting documents, for providing genetic testing.

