# **Study Design**

# **2.1 Methods**

This study will be completed in two stages with two separate cohorts.

Stage 1: Genetic testing and counselling, semi-structured interview, and questionnaires at multiple time points. (n=50)

Stage 2: A one-off questionnaire designed after analysis from stage 1. (n=200)

The cohort for stage 1 of the study will be made up of approximately 50 participants (depending on when data saturation is reached in qualitative analysis of interviews). These participants will all have a suspected inherited risk of melanoma, and will be further stratified into 3 groups for data analysis, including a) those with a positive CDKN2A mutation, b) those positive for a different mutation for melanoma risk, and c) those where no mutation is found. All groups will receive pre and post genetic education and counselling, questionnaires at multiple time points (see table 2), and will participate in a semi-structured phone interview to discuss their experience with genetic testing and counselling one month after receiving test results.

Interview data will be transcribed and evaluated qualitatively using thematic analysis. Questionnaires will compose of validated instruments (see table 1), and will be analysed as per each scale’s manual and standard procedures. Findings produced by questionnaire and interview analysis will then be used to design a novel questionnaire instrument for capturing psychosocial and behavioural impact of genetic testing has for familial melanoma.

Stage 2 of the study will validate the novel questionnaire instrument in a cross-sectional study, enrolling a second cohort of approximately 200 participants with suspected familial melanoma. This second stage of the study will provide a more complete dataset from which hypotheses and conclusions about the psychosocial and behavioural impact genetic testing has for familial melanoma. This information will be a valuable addition to the current literature and inform genetic testing practices in the future.

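### The randomised provider comparison is called a pilot, but aim 3 and the analysis rule make it an open search for significant differences, with no lead outcome and about 25 participants per arm

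*Protocol*

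**What the plan says.** Four parts of the protocol bear on the status and analysis of this comparison.

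- **Introduction.** After arguing that dermatologists could deliver *CDKN2A* testing, it says the study "will include a pilot study to produce preliminary data to explore this concept".
- **Section 1.2, secondary aim 3.** "Determine whether the person conducting the counselling session (genetic counsellor/dermatologist) affects psychosocial and behavioural outcomes".
- **Dermatologist reporting genetic results.** Stage 1 participants "will be randomised to receive the genetic education, counselling and test reporting by either a genetic counsellor or a dermatologist". Allocation is in blocks, stratified by three classes of family mutation status. Questionnaire data from the whole of Stage 1 "will be used to analyse any significant differences in psychosocial or behavioural outcomes".
- **Data Analysis, 7.1.** Paired t-tests and chi-square tests are named for comparisons involving the three mutation groups. For the provider comparison, the text says only that differences will be analysed too.

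Section 2.1 puts Stage 1 at about 50 participants, with the final number depending on saturation of the interview themes. The protocol gives no effect size, power or allocation ratio for the provider comparison, and singles out no scale or time point for it.

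**The concern.** The Introduction describes a pilot. Aim 3 and the dermatologist section describe a comparison meant to settle a question by finding significant results anywhere in the questionnaire data. Those are different undertakings, and a sample sized for interview saturation suits only the first.

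This is the only randomised comparison in the study, and it bears on who could deliver testing. Two misreadings become possible. One chance result among many tests could be reported as a provider effect. Alternatively, an absence of significant results could be taken as support for dermatologist delivery, when arms this small leave moderate differences in either direction open.

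**Working it through.** The protocol states no figure for this comparison, so there is none to reproduce. The check counts the comparisons that the rule admits and works out what one comparison can show.

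**Count from Table 1.** These are the ticks after baseline in the columns for participants who go on to testing. The Monitor/Blunter scale is left out as a trait measure; including it adds one.

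| Instruments | Cells |
| --- | --- |
| Sun exposure 2, skin surveillance 2, risk perception 4, Health Belief Model 1, HADS 4, Cancer Worry 2, Fatalism 2 (all have a baseline score) | 17 |
| STAI (no baseline score) | 1 |
| Counselling-experience scales: Genomic outcomes 1, GCSS 2, Decision Regret 2, Decision Satisfaction 1, PPC 1, MICRA 3 | 10 |
| **Total** | **28** |

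Without the counselling-experience block the count is 28 − 10 = 18. Testing subscales would raise either figure.

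**False positives if the provider has no effect** (5% two-sided per test, assumed):

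- Expected number: 28 × 0.05 = 1.4, whatever the correlation. With 18 tests: 18 × 0.05 = 0.9.
- Chance of at least one, if independent: 1 − 0.95^28 = 0.76. With 18 tests: 1 − 0.95^18 = 0.60.
- Chance of at least one of 28, simulated with a common correlation (assumed): 64% at 0.3, 49% at 0.5, 33% at 0.7.

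**What one comparison can show** (50 participants, 1:1 assumed, so n = 25 per arm; outcome SD = 1):

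- Standard error of the difference: √(2/25) = 0.283 SD.
- 95% CI half-width: 2.01 × 0.283 = 0.57 SD (t, 48 df).
- Power for 0.5 SD: Φ(0.5/0.283 − 1.96) = Φ(−0.19) = 42%.
- Power for 0.8 SD: Φ(0.8/0.283 − 1.96) = Φ(0.87) = 81%.
- Detectable difference at 80% power: (1.96 + 0.84) × 0.283 = 0.79 SD, or 0.81 SD by the non-central t.
- At a Bonferroni threshold of 0.05/28, power for 0.5 SD is 9%.
- With 20 per arm (20% loss, assumed), power for 0.5 SD is 35%.
- 80% power for 0.5 SD would need 63 per arm.

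**Effect of baseline adjustment on a single lead outcome.** The SD is multiplied by √(1 − r²), where r is the correlation between baseline and outcome (assumed 0.5 to 0.7).

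- r = 0.5: half-width 0.57 × 0.87 = 0.49 SD; power for 0.5 SD is 53%.
- r = 0.7: half-width 0.57 × 0.71 = 0.41 SD; power for 0.5 SD is 70%.

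Adjustment helps, but in this range it does not reach 80% power for 0.5 SD. Estimation remains the realistic goal.

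**The case against.** The strongest reply is that the protocol is already modest. The primary aim is qualitative, the sample size follows from that, and the Introduction uses the word pilot. A power calculation is not normally expected of a pilot inside such a study, and choice of lead scale, multiplicity and covariates can be left to an SAP, which is not at hand. This stands in part: neither the missing power calculation nor the missing model is an error. It does not remove the mismatch, because the verb in aim 3 and the search for any significant difference are both protocol text.

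The count can also be challenged. The protocol does not say that every cell of Table 1 will be tested, and the counselling-experience scales may not all count as psychosocial outcomes. That is fair, so 28 is an upper count with 18 as the narrower one. The 76% figure is likewise the value under independence. Repeated scales in the same people are correlated, so the range down to 33% should be quoted with it. Even 33% is more than six times the nominal 5%.

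A reader might infer three stronger things that the document does not support:

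- **That the plan discards baseline scores and strata.** The paired t-tests and chi-square tests are named for the mutation groups. No test is named for the provider comparison, so nothing is fixed wrongly there.
- **That no provider effect could ever be determined.** A single comparison has about 81% power for 0.8 SD. The limit concerns moderate effects and conclusions of no difference.
- **That the investigators intend to claim equivalence.** No part of the protocol says so. The risk lies in how a null result could be read.

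**Conclusion.** The point holds as an internal mismatch with a practical consequence. The protocol labels the provider comparison a pilot, but aim 3 and the dermatologist section commit it to finding any significant difference, without a lead outcome or time point. Followed as written, the rule allows up to 28 tests and about 1.4 false positives on average under no effect, with a 33% to 76% chance of at least one over correlations from 0.7 to zero. Each comparison is precise only to about ±0.57 SD, so moderate differences can be neither reliably detected nor ruled out.

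These figures assume 1:1 allocation, full follow-up of about 50 participants and two-sided 5% tests. Losses would widen the intervals. Baseline adjustment is a precision gain on offer, not the correction of a protocol error, and only 17 of the 28 cells have a baseline score to use. This is a recommended change to a secondary aim; it does not affect the qualitative primary aim.

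**What to change.** 1. In aim 3, replace *Determine* with *Estimate*, so that it agrees with the pilot status in the Introduction.
2. In the dermatologist section, replace the search for significant differences with wording such as: *The provider comparison is exploratory. One lead outcome at one time point, chosen by the investigators before analysis from the scales with a baseline score, is compared by allocated arm, adjusted for its baseline score and the family-mutation stratum (sparse strata combined), and reported as a difference with a 95% CI. All other scales are reported as exploratory estimates with 95% CIs. A non-significant result is not read as equivalence.*

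The choice of lead outcome belongs to the investigators, since the protocol does not rank the scales.

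The cost is a wording change. The baseline scores are already collected and the strata are already defined for randomisation, so no extra participants, visits or questionnaires are needed. The drawback is a more modest claim for aim 3.

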## **Assessment of clinician training protocol**

To evaluate the success, and identify areas that require improvement, clinicians trained to provide genetic testing for this study will be interviewed. A semi-structured interview guide will be used to cover two topics, a) the training process, including the supporting documents and aids, and b) usefulness of genetic testing for familial melanoma. Audio recordings of the interviews will be transcribed verbatim, and used for thematic analysis following methods described in section 8.1.

- - 1. Recruitment of Clinicians for Interviews

To date (August 2021) there have been 8 clinicians trained to provide genetic test results. Any future trained clinicians may also be contacted about interview participation. Clinicians will be contacted via a short email, with the attached PICF. If no response to the email is received, then a follow up email will be sent 2 weeks later. A copy of standardised email recruitment text is provided in a separate document.

- - 1. Procedure for Clinician Interviews

Prior to interviews proceeding, Associate Investigator [name] will discuss the PICF with clinicians, answer any questions they have, and gain written consent if they are willing. [name] will then conduct the interviews at a time and place that is convenient for the Clinicians. If the clinician prefers to do the interview by phone, that will be arranged. If the clinician prefers to just answer the questions in text, rather then talking, then an email of the list of questions will be sent to the clinician. The clinician can then type their answers and email them back. Phone or in-person interviews will be audio recorded for later transcription. Transcription will be done by a professional contracted transcribing service.

- - 1. Sample Size and Analysis of Clinician Interviews

Interview transcripts will be used for qualitative analysis, using methods of thematic analysis (as described in section 8.1). The aim of qualitative research is to uncover a variety of opinions. There is no calculation used to determine sample size for qualitative research. The aim is to reach ‘saturation’ in new themes or perspectives found in the interview transcripts. For narrow research themes, such as the current study, saturation is often reached after around 10 participants. Our intention is to publish the results of the Clinician Interviews, and present at conferences. All clinicians trained in this study will be invited to co-author publications, regardless of whether they participate in the clinician interviews or not.

